## Abstract

**Background:**

Providing timely access to physiotherapy has long been a problem for the National Health Service in the United Kingdom. In an attempt to improve access some physiotherapy services have introduced a new treatment pathway known as PhysioDirect. Physiotherapists offer initial assessment and advice by telephone, supported by computerised algorithms, and patients are sent written self-management and exercise advice by post. They are invited for face-to-face treatment only when necessary. Although several such services have been developed, there is no robust evidence regarding clinical and cost-effectiveness, nor the acceptability of PhysioDirect.

**Methods/Design:**

This protocol describes a multi-centre pragmatic individually randomised trial, with nested qualitative research. The aim is to determine the effectiveness, cost-effectiveness, and acceptability of PhysioDirect compared with usual models of physiotherapy based on patients going onto a waiting list and receiving face-to-face care. PhysioDirect services will be established in four areas in England. Adult patients in these areas with musculoskeletal problems who refer themselves or are referred by a primary care practitioner for physiotherapy will be invited to participate in the trial. About 1875 consenting patients will be randomised in a 2:1 ratio to PhysioDirect or usual care. Data about outcome measures will be collected at baseline and 6 weeks and 6 months after randomisation. The primary outcome is clinical improvement at 6 months; secondary outcomes include cost, waiting times, time lost from work and usual activities, patient satisfaction and preference. The impact of PhysioDirect on patients in different age-groups and with different conditions will also be examined.

Incremental cost-effectiveness will be assessed in terms of quality adjusted life years in relation to cost.

Qualitative methods will be used to explore factors associated with the success or failure of the service, the acceptability of PhysioDirect to patients and staff, and ways in which the service could be improved.

**Discussion:**

It is still relatively unusual to evaluate new forms of service delivery using randomised controlled trials. By combining rigorous trial methods with economic analysis of cost-effectiveness and qualitative research this study will provide robust evidence to inform decisions about the widespread introduction of PhysioDirect services.

**Trial registration:**

Current Controlled Trials ISRCTN55666618

## Background

### The scale of the problem

Musculoskeletal problems are very common, accounting for 15% of all consultations with general practitioners (GPs) in the United Kingdom (UK) [1]. Many of these patients are referred to physiotherapists, with 4.4 million new referrals to physiotherapy being made each year [2]. Ensuring timely access to physiotherapy has long been an issue within the NHS, with waiting times for treatment of several months in some areas. This is a problem for patients, because musculoskeletal conditions cause pain and disability, and for the economy because these conditions are second only to mental health problems as a cause of days lost from work. In particular, back pain accounts for some 120 million days of certified absence from work each year and half of all patients with back pain who are off work for more than 6 months never return to employment [3]. Delayed access to physiotherapy is also a problem for the NHS because when patients are finally offered a physiotherapy appointment many fail to attend, and in other cases patients wait a long time for a physiotherapy consultation when it is unlikely that this will offer benefit, so much of the current physiotherapy resource is used inefficiently and ineffectively.

### PhysioDirect as a new way of improving access to care

In response to these problems, several areas in the UK have introduced a new form of treatment pathway, known as 'PhysioDirect'. In this approach, patients seeking physiotherapy are invited to telephone a physiotherapist for an initial assessment and advice, following which the patient is posted written self-management and exercise advice. Patients are invited for a face-to-face consultation if the initial telephone assessment establishes that this is necessary or if the patient does not get better after following the initial advice.

PhysioDirect is based on a physiotherapist following a computerised algorithm to assess the patient in a structured way, and offering appropriate written advice. This reflects a wider trend to explore the use of this type of technology in health care, exemplified by the development of NHS Direct within the UK. Although there is little evidence about the role of telephone assessment in the context of physiotherapy, research on the use of telephone triage systems in other clinical settings has shown that it is safe, clinically accurate, cost-effective, acceptable to patients, and reduces the workload of clinicians [4-7].

### The effectiveness of physiotherapy

Research about the effectiveness of alternative approaches to provision of physiotherapy services needs to take account of the evidence about the effectiveness of different forms of physiotherapy in different conditions. For some conditions (for example acute low back pain) it appears that manual physiotherapy offers little benefit over simple advice. In conditions such as chronic back pain, promoting exercise appears to be effective [8-11], while systematic reviews about the effectiveness of manipulation have reached inconsistent conclusions [12,13]. Importantly, recent trials have shown that a single session of advice from a physiotherapist is as effective as a course of routine physiotherapy for patients with mild to moderate back problems [14,15] Similarly, several recent trials have shown that physiotherapy-led advice and exercise are effective in knee pain [11,16,17]. On the other hand, for some other conditions such as neck pain and shoulder pain there is evidence that adding manual physiotherapy interventions to advice and exercise is more effective than advice and exercise alone [18-20].

In summary, it is becoming clear that for some conditions patients may benefit from physical treatment such as exercise and manual therapy from a physiotherapist, for other conditions it is equally effective and may be cheaper to provide brief advice about self-management and exercise, and in some situations physical treatments from physiotherapists have little to offer. Therefore the concept of an approach which provides assessment, advice and triage initially and reserves more intensive (and expensive) treatments for those who do not improve may be the most cost-effective strategy. This is analogous to the 'stepped care' approach which is increasingly advocated in a range of conditions, for example mental health, where there is a high level of demand and a need to target resources. In the context of physiotherapy, this approach could reduce costs for patients and for the NHS, provide earlier advice for all patients and physical treatment more quickly for those who may benefit from it (by screening out those unlikely to benefit from it), and be more convenient and accessible for patients as a whole.

### Is faster access beneficial?

The drive to provide faster access to physiotherapy is predicated on the assumption that providing treatment at an earlier stage is beneficial compared with delayed treatment. There is evidence from several studies that early physiotherapy intervention in some situations provides faster symptom relief, improves quality of life, reduces absenteeism, leads to a reduction in physician consultations, and is more cost-effective [21-24].

### Existing evidence about PhysioDirect

Local evaluations and one small trial of PhysioDirect suggest that services based on telephone advice given by physiotherapists are likely to be popular with patients [25], although there is no evidence about costs or outcomes, or the important issue of safety. Audits in the pioneering services in Cheltenham and Huntingdonshire suggested that 40–60% of patients referred by GPs to physiotherapy can be managed by telephone alone without a face-to-face consultation, telephone consultations take approximately half as long as face-to-face consultations, waiting times for a face-to-face appointment were reduced from four weeks to 10 days and 'did-not-attend' (DNA) appointment rates were reduced from 15% to 1%. Patients were very satisfied with the service, with 80% rating it as good or excellent [25-27]. These findings demonstrate the potential benefits of PhysioDirect, but the lack of comparative data from concurrent controls, and a lack of robust data about clinical outcomes and costs, means that there is insufficient evidence currently available to justify the widespread implementation of this new way of working.

### Research questions

This paper describes the protocol for a randomised controlled trial of 'PhysioDirect' versus usual care based on patients going onto a waiting list for a face-to-face appointment.

The research questions are:

• Is PhysioDirect at least as effective as usual models of physiotherapy based on patients going onto a waiting list for face-to-face physiotherapy?

• What is the cost-effectiveness of PhysioDirect compared with usual care?

• Do patients prefer PhysioDirect services rather than usual care; do they find PhysioDirect more convenient and does it address their perceived needs?

• What are the health outcomes and experiences of different groups of patients (those in different age groups and with different types of problems) when referred to PhysioDirect rather than usual care?

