### Analysis

The main hypotheses are that PhysioDirect will be clinically equivalent to usual care and more cost-effective at 6 months after randomisation.

Analysis and presentation of data will be in accordance with CONSORT guidelines. The *primary analysis *will employ multivariable regression to investigate between-group differences in mean SF-36 PCS score at six months follow up. The primary analysis will be conducted on an intention-to-treat (ITT) basis, with due emphasis placed on the confidence interval for the between-arm comparison when inferring equivalence (or otherwise) of the two groups. Clinical equivalence between the arms will only be concluded if the 95% confidence interval for the primary outcome lies wholly inside the range -0.2 to 0.2 SDs. Given the equivalence design and the generally conservative nature of ITT analysis, between-group differences will also be investigated using methods that model compliance with the allocated treatment arm, such as instrumental variable regression. Analyses will adjust for minimisation variables and baseline outcome variable scores, and will take appropriate account of the hierarchical nature of the data (practice and physiotherapy site).

In the *economic analysis *mean cost to the NHS per patient in each arm will be compared with mean gain in quality adjusted life year (QALY) using the EQ5D in order to estimate a cost-utility ratio of incremental cost per QALY gain. Secondary analysis will explore the QALY gain using the SF-6D [34], derived from the SF-36. A cost-consequences matrix will be used to present a comparison of cost per patient in each group from the patient and societal perspectives with a range of outcomes, for example, personal perception of improvement and patient satisfaction. The effect of uncertainty in unit cost estimates or assumptions about resource use will be addressed in sensitivity analyses. Using a bootstrapping approach for data analysis, the results of the economic analysis will be presented using cost-effectiveness acceptability curves.

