### Sample size and power calculations

This study is powered to establish clinical equivalence using the PCS scale from the SF-36. The minimum clinically important difference in a range of populations and conditions has been estimated as being at least 4 points (0.4 SD) [35-38]. However in this study a difference of no greater than 2 points has been specified as demonstrating equivalence. This is equivalent to an effect size of 0.2, which is considered a small effect size [38]. Sample sizes for analysis of 488 and 976 in the Usual Care and PhysioDirect groups respectively will yield 80–95% power to reject a null hypothesis of non-equivalence with an overall alpha of 0.05 alpha assuming that the observed difference in means is in the range zero to 0.045 SDs. The target sample size for patients completing the final six-month follow-up questionnaire is 1000 patients in the PhysioDirect arm and 500 patients in the Usual Care arm.

Assuming 20% non-collection of the primary outcomes, it will be necessary to recruit 1250 and 625 patients in the PhysioDirect and usual care arms respectively, or 1875 patients in total.

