### Establishing equivalence or difference

Most randomised controlled trials test a hypothesis of a difference between groups by disproving a null hypothesis of no difference. In this trial, it is unlikely that PhysioDirect would provide better clinical outcomes than usual care in the long term. Instead the hypothesis is that PhysioDirect would provide equally good clinical outcomes in the long term, while being more cost-effective, providing a faster recovery and return to work and providing important benefits in secondary outcomes such as patient satisfaction and waiting times. For this reason the study is designed as an equivalence trial (to assess equivalence in the primary outcome of clinical outcome at 6 months) while also assessing difference in cost-effectiveness and the secondary outcomes.

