### Appropriate outcome measures

In planning this study, there was much discussion about the most appropriate primary outcome and how this should be measured. It was decided to use clinical outcome as the primary outcome for the reasons described below. However, it could be argued that the main purpose of this type of service is to improve cost-effectiveness, and that effectiveness should not be considered without consideration of cost. Just as it is important to consider whether the extra cost of a new and more effective service can be justified in terms of cost per QALY, it is arguable that a new service such as PhysioDirect may be justifiable even if it is slightly *less *effective than usual care, if it is considerably less expensive, and if the extra cost per QALY of usual care is above the threshold used to determine the acceptability of new treatments.

It was decided to use clinical outcome rather than cost-effectiveness as the primary outcome for several reasons. First, it is clearly important to establish whether a new service is at least as effective as an existing service, and at present (rightly or wrongly) it is conventional to assess whether a new treatment is effective before considering issues of cost-effectiveness. Second, the arguments described above about the application of findings with regard to cost-effectiveness are controversial [39]. Third, there are various methodological issues relating to the use of cost-effectiveness as a primary outcome which remain unresolved or introduce large elements of uncertainty (for example, assumptions needed to calculate sample size).

The traditional trial paradigm which places great emphasis on defining a primary outcome has limitations in relation to the evaluation of health service innovations. In reality, policy decisions about the implementation of new services will be based on taking into account all of the different benefits and costs. Different stakeholder groups such as patients, health service managers or physiotherapists, will place different values on different outcomes (for example, managers may place more value on cost and patients on subjective experience).

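### Research question 1 is one-sided but the only primary decision rule is two-sided equivalence, so an interval above −0.2 SD that extends beyond +0.2 SD has no pre-specified reading

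*Protocol article*

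**What the plan says.** Under Research questions, the protocol article first asks: "Is PhysioDirect at least as effective as usual models of physiotherapy based on patients going onto a waiting list for face-to-face physiotherapy". The Discussion (Appropriate outcome measures) uses the same one-sided idea when explaining why clinical outcome was made primary: "it is clearly important to establish whether a new service is at least as effective as an existing service".

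The Analysis section states the hypothesis differently: "The main hypotheses are that PhysioDirect will be clinically equivalent to usual care". Its single decision rule for the primary outcome, SF-36 PCS at six months, is that clinical equivalence will "only be concluded if the 95% confidence interval for the primary outcome lies wholly inside the range -0.2 to 0.2 SDs". The same section says that due emphasis will be placed on the confidence interval when inferring equivalence or its absence.

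The choice is explained under Establishing equivalence or difference: "it is unlikely that PhysioDirect would provide better clinical outcomes than usual care in the long term", so the trial is designed to show equally good long-term outcomes together with gains in cost-effectiveness and secondary outcomes. Sample size and power calculations fixes the margin, since "a difference of no greater than 2 points has been specified as demonstrating equivalence", and equates it with an effect size of 0.2.

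The article nowhere says how an interval that clears −0.2 SD but extends beyond +0.2 SD would be read against question 1.

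**The concern.** Whether a new service is at least as good as the old one depends only on the confidence limit on the unfavourable side. The printed rule also requires the favourable limit to stay inside the margin. The rule is therefore stricter than the question, and the two come apart when PhysioDirect does somewhat better than usual care. Equivalence is then not concluded, and no other conclusion has been specified in advance.

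What is at stake is the pre-specified answer to the first research question. The estimate, its interval and the error rate of the equivalence claim are unaffected. A reader could still see from the interval that PhysioDirect was not materially worse, but would be drawing that conclusion after the fact.

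**Working it through.** **Inputs.** All come from Sample size and power calculations and Analysis: 488 usual care and 976 PhysioDirect patients analysed; margin 0.2 SD, stated as 2 PCS points, so 1 SD = 10 points; 95% interval; planning difference 0 to 0.045 SD; stated power 80–95%. Let d be the true difference, PhysioDirect minus usual care, in SD units, with higher PCS better. The article does not state this direction.

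**Precision.** SE = √(1/488 + 1/976) = 0.0554 SD. Half-width of the 95% interval = 1.96 × 0.0554 = 0.109 SD (1.09 points).

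**The article's own power figure.**
- Against one margin only, at one-sided 0.025, power = Φ((0.2 − |d|)/SE − 1.96), taking the difference as lying towards that margin. This gives 95.0% at 0 and 79.8% at 0.045, so both ends of 80–95% are reproduced.
- The printed rule needs both limits inside, so power = Φ((0.2 − d)/SE − 1.96) + Φ((0.2 + d)/SE − 1.96) − 1. At d = 0 this is 2 × 0.9503 − 1 = 90.1%. At d = 0.045 it is 0.798 + 0.993 − 1 = 79.1%. The lower end is reproduced; the upper end is not.
- At the follow-up target of 500 and 1000, the printed rule gives 80.2% to 90.9%.

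**Where rule and question part.** The upper limit passes +0.2 SD once the observed advantage exceeds 0.2 − 0.109 = 0.091 SD (0.91 points). At that point the lower limit is 0.091 − 0.109, about −0.017 SD before rounding, far above −0.2. Once the observed advantage exceeds 0.109 SD the interval also excludes zero in favour of PhysioDirect, and the rule is still not met.

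**How often.** The chance that the lower limit alone clears −0.2 SD is Φ((0.2 + d)/SE − 1.96). Its excess over the equivalence probability is the chance of landing in the gap (differences taken before rounding).

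| True d (SD) | Equivalence rule met | Lower limit above −0.2 SD | Gap (points) |
|---|---|---|---|
| −0.045 | 79.1% | 79.8% | 0.7 |
| 0 | 90.1% | 95.0% | 5.0 |
| +0.045 | 79.1% | 99.3% | 20.2 |
| +0.10 | 43.8% | >99.9% | 56.2 |
| +0.15 | 14.5% | about 100% | 85.5 |

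The last two rows lie outside the planning range of 0 to 0.045 SD.

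**The case against.** The strongest reply is that equivalence was chosen openly and with a reason. The Analysis, Sample size, Sub-group analyses and Discussion sections all use it consistently, so the mismatch comes down to the wording of one background question. The sentence in Appropriate outcome measures explains a choice of outcome and sets no decision rule. This stands. The reason given, however, explains why superiority was not planned for; it does not explain why a favourable limit is needed to answer a one-sided question.

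A reader might infer that a modestly better PhysioDirect result counts as a failure. The article does not say so. It says only that equivalence would not be concluded, which is correct when a difference beyond the margin has not been excluded.

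A reader might also infer that the trial cannot answer its first question. That is too strong, because an interval wholly inside ±0.2 SD necessarily has its lower limit above −0.2 SD.

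The one-sided formula reproduces both ends of the stated power, so it is tempting to conclude that the trial was really sized for non-inferiority. The article says that it was powered for equivalence, and the match may simply reflect a calculation that ignored the second margin.

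Finally, the reading of each interval position may be set out in a full protocol or analysis plan that is not shown. That could close the gap. It would not remove the difference in direction between the question and the rule as the article prints them.

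**Conclusion.** The point holds in a limited form. Question 1 is one-sided and the only primary rule is two-sided. An interval above −0.2 SD that extends beyond +0.2 SD therefore leaves question 1 without a pre-specified answer, although the data support yes.

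Within the planning range, the chance of that outcome is about 5% at no true difference and about 20% if PhysioDirect is truly 0.045 SD better. It is under 1% if PhysioDirect is 0.045 SD worse. It exceeds one half at a true advantage of 0.10 SD, but that is beyond the planning range and in a direction the article considers unlikely in the long term.

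These figures assume a normal approximation, an SD of 10 points, no precision gained from covariate adjustment and none lost to clustering. Severity is minor to moderate.

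**What to change.** In the Analysis section, define the difference as PhysioDirect minus usual care, with higher PCS better. Then state that question 1 is answered yes if the lower limit of the 95% confidence interval is above −0.2 SD, and that equivalence is concluded in addition only if the upper limit is also below +0.2 SD.

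The equivalence conclusion is nested within the lower-limit conclusion and both read the same interval, so no alpha adjustment is needed. The sample size does not change: at a true difference of zero the lower-limit conclusion has 95% power with 488 and 976 analysed. The cost is two or three sentences.

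If the sponsor wants equivalence and nothing else, rewording question 1 as a question of equivalence removes the inconsistency equally well.

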## Methods

### Study design

The study consists of an individually randomised pragmatic randomised controlled trial with two parallel groups, incorporating economic evaluation and nested qualitative research. The comparison is between patients randomised to a service based on initial telephone assessment and advice from PhysioDirect, followed by face-to-face treatment when necessary, versus usual care consisting of allocation to a waiting list followed by face-to-face care for all patients.

